### 2.3. Sample Size and Randomization

To detect a minimum mean difference of 8.26 in the primary outcome (depression symptoms), with an assumed standard deviation of 9.36, a sample size of 50 participants (25 per group) was calculated. These assumptions were based on the results of Stelzer et al. [38], who conducted an RCT involving individuals with depression undergoing a structured physical exercise psychotherapy intervention. Although their intervention modality was not delivered online, the target population and outcome measure were comparable to those used in the present study. The observed change in depressive symptoms in that trial was considered clinically meaningful and therefore appropriate to inform the sample size estimation in the context of exercise-based interventions for depression. This calculation assumed an alpha error of 0.05 and a statistical power of 85%. To accommodate potential loss to follow-up, 80 participants were initially recruited, accounting for a possible dropout rate. This ensures sufficient statistical power for the SONRIE study throughout its duration.

Participants were randomized in a 1:1 ratio to either the Experimental Group (EG; n = 40) or Control Group (CG; n = 40), ensuring balance in sex, age, and clinical severity of depression. The randomization process was conducted using a computer-generated sequence through STATA version 16.0 (Stata Corp, College Station, TX, USA). To prevent selection bias, allocation concealment was ensured by using a centralized randomization procedure, where the sequence was generated and stored by an independent researcher not involved in recruitment, intervention, or data collection. Group assignments were only revealed to participants after baseline assessments were completed, ensuring that neither researchers nor participants could predict or influence the allocation process.

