After randomization, four participants from the CG withdrew, leaving 36 participants in this group. Subsequently, the impact of the COVID-19 pandemic led to further attrition, reducing the CG to 25 by the post-intervention assessment and to 16 by the 8-week follow-up. In contrast, the EG showed better retention, with 37 participants remaining at the end of the study. Of these, 30 attended over 80% of the sessions. A flowchart detailing participant progression is presented in Figure 1. The higher dropout rate observed in the CG may be partially explained by reduced motivation in the absence of an active intervention. In addition, elevated attrition is a well-documented phenomenon in digital health trials, especially in the context of self-guided or internet-based interventions. As described in the “law of attrition” [39,40], such patterns are often expected and reflect typical user behavior rather than methodological flaws. Similar adherence challenges have been reported in previous web-based trials for depression and anxiety [39,40].

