### 2.7. Internet-Based Psycho-Physical Exercise Intervention Program

#### 2.7.1. Control Group (CG, Usual Care)

Participants randomly assigned to the CG received standard care throughout the study. This group did not engage in the internet-based psycho-physical exercise intervention program but continued their usual care routines.

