### 2.8. Statistical Analysis

To assess the effectiveness of randomization, baseline (pre-test) values will be compared between the EG and the CG for potential clinically important differences using independent samples *t*-tests for continuous variables and chi-square tests for categorical variables. Effect sizes will be calculated to quantify the magnitude of any differences observed. The difference between groups in the change (pre, post, and 8-week follow-up) of the primary outcome (e.g., depression scores) and all secondary outcomes will be analyzed using Analysis of Covariance (ANCOVA) for continuous outcomes that meet model assumptions. For outcomes that are not continuous or do not meet ANCOVA assumptions, appropriate generalized linear models will be used, specifying the distribution and link function according to the nature of the data (e.g., logistic regression for binary outcomes). The change score will be the dependent variable, with group (EG or CG), time points (e.g., post-intervention, follow-up), and their interaction included as fixed effects. Baseline values and relevant confounding variables (e.g., age, sex) will be included as covariates to adjust for initial differences and control for potential confounders. Model assumptions (e.g., normality, homogeneity of variances, linearity) will be assessed using diagnostic plots and statistical tests. In cases where assumptions are violated, data transformations or non-parametric alternatives will be considered. Effect sizes (with 95% confidence intervals) and statistical significance will be reported for the effects of group (between-subjects), time (within-subject), and the group × time interaction. Partial eta squared (ηp^2^) will be reported for ANCOVA, with effect sizes interpreted as small (ηp^2^ ≥ 0.01), medium (ηp^2^ ≥ 0.06), and large (ηp^2^ ≥ 0.14) according to Cohen’s guidelines [84,85]. Statistical significance will be set at *p* < 0.05. To address the issue of multiple comparisons, *p*-values will be adjusted using the Bonferroni correction [86]. The primary analysis will follow a per-protocol approach, including only participants who attended at least 80% of the intervention sessions. Missing data will be handled using an intention-to-treat (ITT) approach, ensuring that all randomized participants are included in the analysis. A dropout analysis will be conducted to determine whether participants who withdraw differ significantly from those who complete the study. Additionally, sensitivity analyses will be performed to confirm the robustness of the results under various assumptions about missing data. As high attrition is common in internet-based interventions for depression [39,40], these strategies are essential to reduce the risk of attrition bias and preserve internal validity [87]. All statistical analyses will be performed using STATA version 16.0 (StataCorp LP, College Station, TX, USA).

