
## 3. Discussion

The SONRIE study presents an innovative approach to treating mild-to-moderate depression by integrating an online physical exercise program with iCBT. This integration, pioneering in its online format, addresses both the psychological and physiological aspects of depression, with the potential to overcome geographical and social barriers, that limit access to traditional therapy. The relevance of this study is heightened in the current context, where the COVID-19 pandemic and restrictions on face-to-face intervention [88] have driven the need to remote health care solutions. The SONRIE study, by utilizing online platforms for intervention delivery, aligns with this emerging need [31,32] and offers a viable alternative for individuals unable to access face-to-face therapy [89].

Integrating physical exercise with iCBT within an RCT framework represents a significant methodological contribution to the scientific literature. Unlike previous studies that have focused on combined physical exercise and CBT interventions in person [90,91], the online approach of our study facilitates greater flexibility and reach, potentially enhancing adherence and long-term outcomes. The study design enables the examination of the synergistic effects between physical and psychological interventions, providing a scalable model adaptable for diverse populations. Nevertheless, a challenge commonly reported in digital interventions is participant attrition, particularly in control groups not receiving active treatment [39,40]. Anticipating this, our analysis plan includes intention-to-treat and sensitivity approaches to address potential attrition bias and ensure the robustness of future findings [87]. Furthermore, the use of validated assessment tools ensures the generation of reliable and consistent data to evaluate the impact of the intervention on mental and physical health outcomes. The SONRIE study has the potential to serve as a model for future research and clinical practice, demonstrating how combined online interventions can effectively address depressive symptoms and expand the research and effectiveness of mental health services.

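### The primary analysis is per-protocol on a session-attendance rule that can act only on the experimental arm, so it is not the randomised comparison and does not agree with the all-randomised statement that follows it

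*Protocol article*

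**What the plan says.** Section 2.8 (Statistical Analysis) fixes the primary population: "The primary analysis will follow a per-protocol approach, including only participants who attended at least 80% of the intervention sessions". The sentence directly after it reads: "Missing data will be handled using an intention-to-treat (ITT) approach, ensuring that all randomized participants are included in the analysis". Nothing in 2.8 assigns intention-to-treat (ITT) to a secondary or supportive role. The Discussion (section 3) then tells the reader that "our analysis plan includes intention-to-treat and sensitivity approaches to address potential attrition bias".

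Section 2.7.1 says of the control group: "This group did not engage in the internet-based psycho-physical exercise intervention program". No attendance or protocol-adherence rule for controls appears anywhere in the article.

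Section 2.3 gives the counts. Forty participants were randomised to each arm. Of the experimental arm it says: "In contrast, the EG showed better retention, with 37 participants remaining at the end of the study". It continues: "Of these, 30 attended over 80% of the sessions". The control arm fell to 36 after early withdrawals, to 25 at post-test and to 16 at the 8-week follow-up.

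Section 2.7.2 defines adherence separately for each component, with an 80% threshold in both cases: planned sessions for exercise, and modules for the internet-based cognitive–behavioural therapy (iCBT).

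**The concern.** The trial's hypothesis is superiority over usual care. Randomisation supports that claim only if the groups are compared as allocated. Attendance is observed after randomisation and exists in one arm only. Poorly motivated participants can be identified and removed from the experimental arm, but their counterparts among the controls cannot. Attendance plausibly depends on mood and motivation, which may also predict change in BDI, so the participants kept may differ in prognosis from the arm that was randomised.

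The article also gives two answers to the question of who is in the analysis. A reader cannot tell which one produces the headline estimate and p-value. The attendance set is not fully defined either, because the rule does not say whether intervention sessions means exercise sessions, iCBT modules or both.

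**Working it through.** **1. The plan's own sample size.** Inputs from section 2.3: difference 8.26, SD 9.36, alpha 0.05 (two-sided assumed), power 85%. A two-sample t-test (noncentral t) has power 84.9% at 24 per arm and 86.4% at 25 per arm. The stated 25 per arm is reproduced and is not in dispute.

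**2. Who the primary rule keeps (counts from section 2.3).**

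| Arm | Randomised | Kept |
|---|---|---|
| Experimental | 40 | 30 meet the attendance rule: 30/40 = 75% |
| Control, post-test | 40 | 25, by retention only: 25/40 = 62.5% |
| Control, follow-up | 40 | 16, by retention only: 16/40 = 40% |

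The experimental arm loses 40 − 30 = 10. Of these, 40 − 37 = 3 were not retained and 37 − 30 = 7 were retained but fell short on attendance. At least 10 of 80 randomised participants are therefore excluded, which is incompatible with including all of them. (Section 2.3 counts those over 80%, while 2.8 says at least 80%, so 30 could shift slightly if anyone attended exactly 80%.)

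**3. What the attendance filter alone could do, with no treatment effect.** Assume attendance propensity and BDI improvement are bivariate normal with correlation r. The document does not give r. Keeping the top 75% shifts the experimental mean by r × SD × φ(z)/0.75, where φ(z)/0.75 = 0.424. The standard error for 30 v 25 is 9.36 × √(1/30 + 1/25) = 2.53. Two-sided type I error is P(|Z + shift/2.53| > 1.96), treating control loss as ignorable.

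| r (assumed) | Shift favouring intervention, BDI points | Type I error |
|---|---|---|
| 0.1 | 0.40 | 5.3% |
| 0.2 | 0.79 | 6.1% |
| 0.3 | 1.19 | 7.6% |
| 0.5 | 1.98 | 12.3% |

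Allowing for the smaller variance in the truncated arm moves the last figure to 12.7%.

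**4. The same formula applied to control retention.** Keeping the top 62.5% gives φ(z)/0.625 = 0.607. If better-prognosis controls are the ones who stay, with the same r, the control mean improves by:

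- r = 0.1: 0.1 × 9.36 × 0.607 = 0.57; net 0.40 − 0.57 = −0.17
- r = 0.3: 0.3 × 9.36 × 0.607 = 1.70; net 1.19 − 1.70 = −0.51
- r = 0.5: 0.5 × 9.36 × 0.607 = 2.84; net 1.98 − 2.84 = −0.86

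On these assumptions the net bias runs against the intervention. If instead improving controls were the ones who left, the two biases would add.

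**5. Is power a reason to keep the rule?** Nominal power at 8.26 and SD 9.36, taking the 37 retained participants as assessed at both times:

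| Time | Attendance set | All assessed |
|---|---|---|
| Post-test | 30 v 25: 89.2% | 37 v 25: 91.8% |
| Follow-up | 30 v 16: 79.6% | 37 v 16: 82.5% |

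The attendance restriction costs a little power and gains none.

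**The case against.** The best defence is that the authors meant per-protocol as the main analysis and ITT as support, and that the adjacent sentences simply compress this. The text does not say so. It attaches ITT to missing data in the analysis without qualification. Even on that reading, the headline result would still come from a non-randomised set.

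Three stronger readings are tempting and are not supported.

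- A reader might infer that the rule removes every control and leaves no comparison. Taken literally it does, but section 2.8 models group with both arms named, so controls are plainly meant to be analysed. The point rests on the one-arm filter.
- A reader might infer that the bias must favour the intervention. That holds for the attendance filter alone if attendance goes with improvement. The available controls are also selected, more heavily by proportion (62.5% against 75%), and section 2.3 links their dropout partly to reduced motivation. Step 4 shows that this can reverse the sign.
- A reader might infer that the two adherence definitions in 2.7.2 contradict each other. They do not: each covers its own component, and 2.7.2 also calls the iCBT units sessions. What remains is ambiguity in 2.8 about how the two combine.

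The objection that ITT by name does not repair the comparison also stands. With 15 of 40 controls missing at post-test and 24 of 40 at follow-up, the result will depend on how the missing outcomes are handled.

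**Conclusion.** The point holds and needs correcting before results are reported. The article itself names a primary population that is filtered on attendance in one arm (40 to 30, with 7 retained participants set aside), gives no rule for controls, and follows it with an unreconciled statement that everyone randomised is included. Because the article fixes this choice, it is not a detail left to an unseen analysis plan.

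The defect does not depend on any assumed correlation, but its numerical effect does. For r from 0.1 to 0.5, the attendance filter alone contributes about 0.4 to 2.0 BDI points towards the intervention, with type I error of about 5% to 12% for 30 v 25 if control loss is ignorable. Control attrition could offset, reverse or add to this, so the net size and direction of bias are unknown.

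**What to change.** In section 2.8:

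- Make the primary BDI analysis the comparison of all 80 participants as randomised, using every observed post-test and follow-up value.
- Name the missing-data method, for example a likelihood-based mixed model for repeated measures or multiple imputation, with sensitivity analyses under missing-not-at-random assumptions.
- Keep the 80% set as a supportive analysis, labelled as not a randomised comparison. State whether exercise sessions, iCBT modules or both count, and that controls are retained. The count of 30 should be rechecked against whichever definition is adopted.
- Bring the Discussion's description of the plan into line.

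No new data are needed, and nominal power at post-test stays above the planned 85%. The estimate may be smaller than the per-protocol one. The study was completed in October 2020 (section 2.1), and attendance and attrition are already known, so the change must be reported as made after trial completion, with its date and reason.

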
## 3. Discussion

The SONRIE study presents an innovative approach to treating mild-to-moderate depression by integrating an online physical exercise program with iCBT. This integration, pioneering in its online format, addresses both the psychological and physiological aspects of depression, with the potential to overcome geographical and social barriers, that limit access to traditional therapy. The relevance of this study is heightened in the current context, where the COVID-19 pandemic and restrictions on face-to-face intervention [88] have driven the need to remote health care solutions. The SONRIE study, by utilizing online platforms for intervention delivery, aligns with this emerging need [31,32] and offers a viable alternative for individuals unable to access face-to-face therapy [89].

Integrating physical exercise with iCBT within an RCT framework represents a significant methodological contribution to the scientific literature. Unlike previous studies that have focused on combined physical exercise and CBT interventions in person [90,91], the online approach of our study facilitates greater flexibility and reach, potentially enhancing adherence and long-term outcomes. The study design enables the examination of the synergistic effects between physical and psychological interventions, providing a scalable model adaptable for diverse populations. Nevertheless, a challenge commonly reported in digital interventions is participant attrition, particularly in control groups not receiving active treatment [39,40]. Anticipating this, our analysis plan includes intention-to-treat and sensitivity approaches to address potential attrition bias and ensure the robustness of future findings [87]. Furthermore, the use of validated assessment tools ensures the generation of reliable and consistent data to evaluate the impact of the intervention on mental and physical health outcomes. The SONRIE study has the potential to serve as a model for future research and clinical practice, demonstrating how combined online interventions can effectively address depressive symptoms and expand the research and effectiveness of mental health services.

However, certain challenges are anticipated. The reliance on self-reported measures may introduce reporting biases [87], and the requirement for participants to have internet access and digital literacy may limit the generalizability of the findings to populations with limited technological resources. Future studies should consider strategies to include these populations, such as providing technological support or utilizing alternative delivery methods.

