Recent evidence suggests that the endocannabinoid system (ES) plays a critical role in modulating depressive symptoms [12], emotional processing [13,14,15], and neuroplasticity, particularly through its influence on brain-derived neurotrophic factor (BDNF) [12,16]. Dysfunctions in ES signaling, due to genetic factors or pharmacological disruptions, can contribute to depressive-like symptoms [17,18]. Notably, depressed individuals often exhibit lower plasma levels of endocannabinoids (eCBs) and their analogs, supporting the hypothesis of an endocannabinoid deficiency in depression [19,20]. Physical exercise may help counteract this deficiency by increasing circulating eCBs [21,22], especially anandamide (AEA) and 2-arachidonoylglycerol (2-AG), which act predominantly through CB1 receptors in brain regions and CB2 receptors in immune tissues [18]. Through these interactions, eCBs help regulate mood and stress response [12,16,23]. Despite these promising associations, existing research on the exercise-induced modulation of ES biomarkers in depressive disorders remains largely pre-clinical or observational, emphasizing the need for well-designed clinical studies [24,25]. Therefore, exploring the interplay between physical exercise, ES modulation, and BDNF signaling could offer valuable insights into novel therapeutic approaches.

Furthermore, internet-based cognitive–behavioral therapy (iCBT) has demonstrated efficacy in reducing depressive symptoms, improving emotional regulation, and facilitating cognitive flexibility in individuals unable or unwilling to engage in face-to-face interventions [26,27] through digital methods [28,29]. The internet-based delivery of CBT can significantly enhance treatment accessibility and adherence, addressing common barriers such as geographic limitations or reluctance to participate in face-to-face therapy [30,31]. The combination of physical exercise and iCBT, therefore, holds significant promise, potentially offering synergistic benefits by simultaneously addressing the biological, psychological, and behavioral dimensions of depression [32]. Prior studies have successfully combined physical activity with psychological interventions such as mindfulness, demonstrating robust improvements in emotional regulation and overall psychological health [7,10,11,33,34,35]. Nevertheless, the effectiveness and biological underpinnings of combining iCBT and physical exercise interventions delivered entirely online remain unexplored.

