The SONRIE study (ClinicalTrials.gov Identifier: NCT05849792), originally launched in September 2019, is RCT designed to explore the effects of a 12-week online intervention combining iCBT and structured physical exercise in adults diagnosed with mild-to-moderate depression. Although initiated before the global outbreak of COVID-19, subsequent confinement periods have underscored the study’s relevance and applicability in scenarios of isolation. The primary aim of the SONRIE study was to evaluate the immediate and sustained effects of this combined online intervention on depressive symptoms. Additionally, the study has defined secondary objectives: (i) to examine the effects of the intervention on physical health parameters such as body composition, physical fitness, and blood biomarkers including plasma levels of eCBs (AEA and 2-AG) and their analogs or BDNF levels; (ii) to explore its influence on psychological dimensions such as anxiety, stress, emotional states, interoceptive awareness, and overall well-being; (iii) to investigate interrelationships among lifestyle factors including physical activity, sedentary behavior, sleep patterns, and dietary habits, and their predictive value on depressive outcomes; and (iv) to assess the sustainability of the intervention effects during an 8-week follow-up period without further treatment. We hypothesize that participants in the combined intervention group will experience significantly greater reductions in depressive symptoms compared to participants receiving usual care. Secondary hypotheses propose that improvements in depressive symptoms may be associated with positive changes in plasma levels of eCBs and their analogs, and BDNF signaling, alongside improved physical fitness, sleep quality, and emotional regulation. By clearly delineating primary and secondary outcomes, the SONRIE study aims to provide robust evidence on the clinical efficacy and biological underpinnings of an integrated, internet-based psycho-physical exercise intervention program for depression.

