#### 2.7.2. Experimental Group (EG, Enhanced Care with Physical Exercise and iCBT)

The psycho-physical exercise intervention implemented in this study refers to a structured and coordinated program that integrates a multicomponent physical exercise protocol with iCBT. Delivered entirely online, this dual approach was designed to address both the physiological and psychological dimensions of depression. The physical exercise component included balance, resistance, and CRF training, individually tailored and progressive, while the iCBT program was based on the Unified Protocol and targeted emotional regulation, cognitive restructuring, and behavioral activation. Both components were scheduled in a complementary manner, with participants viewing the psychological modules prior to each supervised exercise session, thereby enhancing the integrative therapeutic effect of the intervention.

The exercise protocol followed the Consensus on Exercise Reporting Template (CERT) for transparency and replicability [79]. Sessions were conducted by a Physical Educator and Sports Sciences Specialist registered according to Spanish law and holding a Master’s degree in Physical Activity and Health, with initial support provided by a physical therapist. This 12-week exercise program consisted of three weekly sessions: one supervised online session each Tuesday and two asynchronous unsupervised sessions. Sessions were delivered through private YouTube videos, accessible only to study participants, thereby maintaining confidentiality while providing on-demand exercise guidance. Exercise intensity was individually prescribed using the Borg Rate of Perceived Exertion (RPE) scale, targeting moderate to vigorous intensity as recommended by the American College of Sports Medicine’s (ACSM) [80]. Exercise volume adhered to the World Health Organization’s 2020 physical activity guidelines for adults [80].

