Each 60–90 min session began with a 7–10 min warm-up involving dynamic stretches (e.g., arm circles, leg swings) and mobility exercises (e.g., hip rotations, ankle rolls) to gradually increase heart rate and prepare the body for physical activity. The main segment comprised balance, resistance, and CRF training. Balance training lasted 10 min per session, designed to improve coordination, postural control, and core stability. Participants progressed from static balance exercise to dynamic and advanced coordination tasks, maintaining a low perceived intensity (RPE 1–3). Resistance training occupied 25–35 min per session, emphasizing the progressive enhancement of muscular strength, motor control, and core stability. Exercises included squats, lateral and frontal lunges, biceps curls, push-ups, bent-over rows, and shoulder presses structured into 3–4 sets (8–12 repetitions or duration-based sets), following ACSM guidelines [81]. Progression involved increasing time under tension (TUT) principles (from week 4 onwards) and introducing light-to-moderate external weights [82]. The training intensity progressively increased from RPE 3–4 initially to RPE 7–8 by week 12. The CRF training, lasting 13–14 min, included aerobic exercises such as dance aerobics and step routines. Sessions were structured into 2–3 segments of 2 to 9 min each with brief rest intervals (45–60 s). The training intensity started at RPE 3–4 and gradually increased to RPE 7–8 by week 12, designed to achieve 55–89% of the participant’s heart rate reserve, consistent with ACSM recommendations [81]. The sessions concluded with an 8-10 min cool-down period incorporating stretching for major muscle groups, relaxation techniques, and postural adjustments. Participants completed pre- and post-session Google Forms questionnaires for supervised and unsupervised sessions to track attendance and monitor participant safety by collecting information on perceived exertion and satisfaction. The supervising specialist reviewed these responses regularly to detect signs of excessive fatigue, discomfort, injury, or dissatisfaction, and provided personalized support or adjustments to the program as needed. In addition, weekly adherence to the prescribed exercise sessions was monitored by analyzing these logs. Participants who missed sessions or reported difficulties received immediate individualized follow-up from the supervising fitness specialist to ensure ongoing engagement. Successful adherence was defined as completion of at least 80% of planned sessions. (Detailed session structure and progression are available in Table A1).

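### The Discussion says the design can examine synergy between exercise and iCBT, but a two-arm trial of the package against usual care identifies only the package effect

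*Protocol article*

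**What the plan says.** The claim appears once, in section 3 (Discussion): "The study design enables the examination of the synergistic effects between physical and psychological interventions". It is put as a property of the design, without qualification.

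The design itself is set out elsewhere in the article:

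- **Allocation (section 2.3).** "Participants were randomized in a 1:1 ratio to either the Experimental Group (EG; n = 40) or Control Group (CG; n = 40").
- **Experimental arm (section 2.7.2).** The intervention is described as "a structured and coordinated program that integrates a multicomponent physical exercise protocol with iCBT". The iCBT modules are viewed before the supervised exercise sessions.
- **Control arm (section 2.7.1).** "This group did not engage in the internet-based psycho-physical exercise intervention program but continued their usual care routines".
- **Model (section 2.8).** The change score is analysed "with group (EG or CG), time points (e.g., post-intervention, follow-up), and their interaction included as fixed effects", with baseline and confounders as covariates.
- **Primary aim (section 1).** The study is to "evaluate the immediate and sustained effects of this combined online intervention on depressive symptoms".

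Section 1 also mentions synergy, but only as a possibility: the combination is described as "potentially offering synergistic benefits by simultaneously addressing the biological, psychological, and behavioral dimensions of depression". The limitations paragraph that closes section 3 covers self-report and access to technology. It does not say that the components cannot be told apart.

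**The concern.** Synergy between two interventions means that their joint effect differs from what the two separate effects would give. To examine it, the separate effects must be observable, and that takes four conditions: neither, exercise only, iCBT only, and both. This trial randomises only the first and the last.

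The sentence therefore credits the design with a property it lacks. What is at stake is interpretation. A positive result could be cited, on the article's own authority, as evidence that the two components reinforce each other or that both are needed. It would show only that the package as delivered did better than usual care. Nothing in the limitations would check that reading.

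**Working it through.** **Inputs.** From section 2.3: difference 8.26 points on the Beck Depression Inventory (BDI), SD 9.36, alpha 0.05, power 85%, stated size 50 (25 per group). Two-sided testing is assumed because the article does not state it. From sections 2.3, 2.7.1 and 2.7.2: two arms, both components or neither.

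**Step 1: what the stated sample size is for.** With the normal approximation, n per arm = 2 × (SD/difference)² × (z for alpha + z for power)² = 2 × (9.36/8.26)² × (1.960 + 1.036)² = 23.06, rounded up to 24 (48 in total). The two-sample t-test version gives 24.06, rounded up to 25 per arm, which is the stated 50. A one-sided test would give 19 per arm and does not reproduce it. The figure is sound for one contrast, package against usual care, and for no other.

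**Step 2: what the arms identify.** Let E and I be 1 if a participant is assigned exercise and iCBT respectively, and write the mean benefit as

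μ = β0 + βE·E + βI·I + βEI·E·I,

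where βEI is the synergy term. The randomised cells give these rows:

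| Arm | Intercept | E | I | E × I |
|---|---|---|---|---|
| Usual care | 1 | 0 | 0 | 0 |
| Package | 1 | 1 | 1 | 1 |

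The E, I and E × I columns are identical. The rank is 2 for 4 parameters. Testing each contrast against the row space:

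- βE alone: not estimable
- βI alone: not estimable
- βEI alone: not estimable
- βE + βI + βEI: estimable, and equal to the difference between the arms

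A four-cell factorial has rank 4, and all of these become estimable. With only two cells the deficit does not depend on n.

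**Step 3: contact.** The experimental arm also has a weekly supervised session, monitoring by the specialist and psychologist, and, for participants who missed sessions or reported difficulties, individual follow-up (section 2.7.2). A column for this contact would again be 0 for usual care and 1 for the package, so the rank stays at 2, now for 5 parameters. The identified sum absorbs it.

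**Step 4: what an observed difference could mean.** Setting contact aside, take the planned 8.26 points and write it as (βE, βI, βEI):

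- (4.13, 4.13, 0): additive, no synergy
- (0, 0, 8.26): pure synergy
- (8.26, 8.26, −8.26): either component alone would suffice
- (8.26, 0, 0): exercise only

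Each sums to 8.26, and the trial data cannot tell them apart.

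**Step 5: whether anything else in the article supplies the contrast.**

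- The interaction in section 2.8 is group × time. It asks whether the package effect differs between post-intervention and follow-up, not whether exercise and iCBT interact.
- The session-by-session affect scores (PANAS, section 2.7.2) are collected in the experimental arm only, around supervised exercise, with the module viewed just before. They have no comparator for either component.
- Adherence within the experimental arm is not randomised, and 30 of the 37 participants retained attended over 80% of sessions (section 2.3). No synergy analysis based on it is stated.

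**Scale, for illustration only.** In a 2 × 2 factorial with the same SD, alpha and power, the interaction contrast has variance 4·SD²/n per cell. An interaction of 8.26 points would need 4 × (9.36/8.26)² × (2.996)² = 46.1, so 47 per cell and 188 in total. One of 4.13 points would need 185 per cell and 740 in total. The trial randomised 80, in two cells.

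**The case against.** The strongest reply is that this is one clause in a Discussion and nothing operative depends on it. That is correct. The primary aim and hypothesis concern the combined intervention, none of secondary objectives (i) to (iv) mentions synergy or component effects, the sample size is for a single between-group difference, and the model has no component term. Package against usual care is a legitimate design that matches the stated aim. This limits the weight of the point but does not make the sentence true.

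A second reply is that synergistic is loose wording for combined, given the hedged use in section 1 and the promotional tone of the rest of the sentence. This does not fit the words: they speak of effects between two interventions and attribute the capability to the study design. Section 1 hedges and section 3 does not.

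A third is that the detail belongs in a fuller protocol or analysis plan. The point is not an omission, however. It is an affirmative statement, and no analysis plan can make the contrast estimable from these two arms.

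A reader might be tempted to infer more than the article supports:

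- *That a synergy test is planned, or that the primary analysis is compromised by this claim.* Sections 1, 2.3 and 2.8 show neither.
- *That every experimental participant had individual follow-up, making contact a uniform extra treatment.* Section 2.7.2 says that those who missed sessions or had difficulties "received immediate individualized follow-up from the supervising fitness specialist". Contact is still part of the package, through supervision and monitoring, but individual follow-up was conditional.
- *That within-arm dose-response analyses will be used to separate the components.* None is stated. The 80% thresholds define adherence and the per-protocol set.

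**Conclusion.** The sentence is wrong as written. With two randomised arms that differ in both components at once, none of the exercise effect, the iCBT effect or their interaction is estimable at any sample size. Only the sum of the three is identified, together with whatever the programme's supervision and contact contribute. This follows from the allocation alone. It needs no assumption about effect size, variance or retention, and only takes synergy in its ordinary sense of a joint effect that differs from what the separate effects would give.

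The consequence is confined to interpretation. The comparison of the package with usual care, its sample size and its model are untouched by this point. The correction is still worth making: the claim bears on what the trial may conclude, it goes beyond the article's own aims, and the limitations paragraph does not counter it.

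**What to change.** 1. In section 3, delete the clause on synergistic effects, or replace it with a statement such as: *The trial estimates the effect of the combined supervised online exercise and iCBT package compared with usual care.*
2. In the limitations paragraph at the end of section 3, add that the separate effects of exercise and iCBT, any synergy between them, and the contribution of supervision and contact cannot be distinguished in this design.

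The hedged mention of possible synergy in section 1 can stay as rationale. The change takes one or two sentences and no new data or analysis. The study finished in October 2020, so wording is all that can change. The cost is a less favourable interpretive claim.
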